### Sample Size

Each jurisdictional area comprises 1000-5000 individuals. With an approximately annual TB incidence of 130 per 100,000 individuals in Songkhla Province [20], the sample size estimate is based on the assumption that each cluster can recruit approximately 1 to 5 TB patients within 9 months.

This study is designed to detect the cumulative percentage of compliant days of the observers in the VOT group for comparison with those in the DOT group. In development of the VOT, we conducted in-depth interviews of patients with TB and their observers, and discovered that the patients had an actual appointment for DOT only once during the entire follow-up period [7]. According to our previous study [9], the cumulative percentage of compliant days among patients in the VOT group was 65%. We assumed a difference in the cumulative compliance percentage of 64% (65/100–1/60)×100. We accepted 80% statistical power and a significance level of .05 using a one-tailed test. We assumed an intracluster correlation coefficient (ICC) of 0.2. We estimated that each cluster would have approximately three patients during the study. The sample size was calculated using the group-randomized control trial calculator [21]. The variance was set to 1.00 as the default. The formula does not require an exact variance estimation in the population as the ICC takes the variance into account. The required number of clusters for each arm was 19. Thus, the number of TB patients in each group would be 19×3=57. With a sample size inflation factor of 20% to compensate for the uncertainty of TB incidence in each jurisdictional area, a sample size of 70 TB patients is required in each arm.

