**Results:**

The Human Research Ethics Committee, Faculty of Medicine, Prince of Songkla University approved the trial on February 19, 2021 (approval number 64-03618-9). The trial was funded in May 2021. The recruitment period will be from January 2022 to July 2022. The observation is scheduled to end by September 2022.

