### Participants

#### Patients (Individual Level)

Patients will be considered eligible if they have newly active pulmonary TB diagnosed with a positive acid-fast bacilli (AFB) sputum smear, are aged>18 years, own a smartphone, and are able to use the LINE app. Participants are excluded if they have a condition that requires a specialist’s intervention, have rifampicin-resistant TB as tested by GeneXpert, unable or ineligible to continue the treatment for 60 days, or have alcohol dependence.

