## Results

This study is being supported by the Fogarty International Center and the US National Institute of Allergy and Infectious Diseases of the US National Institutes of Health under Award Number D43 TW009522 (June 14, 2021). The researchers and Deputy Province Chief Medical Officer of Songkhla Provincial Public Health Office came to an agreement on the implementation of the VOT on June 22, 2021. Recruitment started in January 2022 and will end in July 2022. The observation period is scheduled to end by September 2022.

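### The patient numbers assume 9 months of every incident TB case, but recruitment runs at most 7 months and takes a consenting, eligible subset; the same arithmetic gives about 43 per arm, not 57 or 70

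*Protocol article*

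**What the plan says.** The Sample Size section starts from cluster populations ("Each jurisdictional area comprises 1000-5000 individuals") and an approximate "annual TB incidence of 130 per 100,000 individuals in Songkhla Province". From these it assumes that "each cluster can recruit approximately 1 to 5 TB patients within 9 months". It settles on about three per cluster and 19 clusters per arm, giving 57 patients per arm. A 20% inflation, said to cover uncertainty in TB incidence, leads to the statement that "a sample size of 70 TB patients is required in each arm".

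The calendar is given twice. The abstract says "The recruitment period will be from January 2022 to July 2022", and the Results section says "Recruitment started in January 2022 and will end in July 2022". The Results section adds "The observation period is scheduled to end by September 2022".

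Eligibility is set out under Participants, Patients (Individual Level). Patients must have "newly active pulmonary TB diagnosed with a positive acid-fast bacilli (AFB) sputum smear", be over 18, own a smartphone and be able to use LINE. Exclusions are rifampicin resistance, alcohol dependence, a condition needing a specialist, and inability to continue treatment for 60 days. Under Cointerventions, only consenting patients are registered.

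**The concern.** The article contains two accrual windows. January to September spans 9 months only if the last patients' 60-day observation is counted, and nobody enrols during that time. The expected yield per cluster also appears to count all TB cases, although the trial admits a subset of them. If both are so, the stated patients per cluster and per arm are not what the stated design delivers. Some primary care units (PCUs) may also supply no patient and contribute nothing to the mixed model. A reader would then be relying on a size, a precision and possibly a power that the plan does not support.

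**Working it through.** **Inputs.** From the Sample Size section: population 1000-5000 per cluster, incidence 130 per 100,000 per year, 19 clusters per arm, three patients per cluster, difference 0.64, variance 1.00, ICC 0.2, one-tailed 0.05. From the abstract and Results: January to July 2022, at most 7 months. Assumed here: mean cluster population 3000, the midpoint of the stated range.

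**Step 1: reproduce the plan's figures.** Expected cases per cluster = population × 130/100,000 × months/12. At 9 months:
- 1000 people: 0.975
- 3000 people: 2.925
- 5000 people: 4.875

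These are the plan's 1, about 3 and 5. Per arm, 19 × 2.925 = 55.6, against the stated 57. The inflated target also reproduces approximately: 57 × 1.2 = 68.4 and 57/0.8 = 71.25, against 70. No factor for eligibility or consent is needed to obtain the plan's numbers, so none was applied.

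**Step 2: use the stated recruitment window.** At 7 months the same formula gives 0.76, 2.28 and 3.79 per cluster. At the midpoint, 19 × 2.275 = 43.2 per arm with every case enrolled. Then 43.2/57 = 0.76 (24% short) and 43.2/70 = 0.62 (38% short).

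**Step 3: what the targets would need.** With every case enrolled:
- Time at 3000 people per cluster: 57/(19 × 3.9) × 12 = 9.2 months; for 70, 11.3 months. So 70 is not the expected yield even of 9 months.
- Mean population at 7 months: 57/(19 × 0.0013 × 7/12) = about 3960; for 70, about 4860, close to the stated maximum of 5000.

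The 20% inflation raises the target but adds no cases, time or clusters.

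**Step 4: power on the plan's own inputs.** Variance of the difference = 2 × [1 + (m − 1) × 0.2]/(m × k), with m patients per cluster and k clusters per arm. Power is from the noncentral t with 2(k − 1) degrees of freedom, one-sided 0.05. The higher power uses k = 19. The lower removes the clusters expected to be empty, a share exp(−mean) (Poisson, equal populations). The enrolled shares of 80% and 50% are assumptions; the documents give none.

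| Scenario | Mean per cluster | Patients per arm | Expected empty PCUs | One-sided power |
|---|---|---|---|---|
| As planned | 3 | 57 | not removed | 88% |
| 7 months, all enrol | 2.28 | 43 | 10% | 82-83% |
| 7 months, 80% enrol | 1.82 | 35 | 16% | 76-78% |
| 7 months, 50% enrol | 1.14 | 22 | 32% | 61-65% |

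**Step 5: precision, whatever the SD.** The standard error scales with the square root of [1 + (m − 1) × 0.2]/(m × k). As planned this is √(1.4/57) = 0.157. For 7 months with all enrolled and k = 19 it is √(1.255/43.2) = 0.170, or 9% larger. At 50% enrolment it is √(1.0275/21.6) = 0.218, or 39% larger. Removing empty clusters makes both somewhat worse.

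**The case against.** Four points can be made for the plan.

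**The targets are not shown to be out of reach.** A reader might infer that 57 or 70 per arm cannot be attained. The documents do not support that. They give a population range, not a mean, and a provincial rate rather than one for the two study districts. If every PCU had 5000 people, 7 months would yield 72.0 cases per arm, so 57 would need 79% enrolled and 70 would need 97%. This stands, and the claim is therefore limited to the provincial rate and the midpoint population.

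**The stated test is one-tailed.** A reader might also infer that shortening the window by itself drops power below 80%. That follows only on a two-sided test (80% falling to 71-73%). On the stated one-tailed test the shorter window leaves 82-83%. There is slack because the stated inputs need only 15 clusters per arm one-sided, while 19 matches a two-sided calculation; that is a separate matter.

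**The power loss depends on a variance of 1.00.** This is a calculator default, whereas a proportion between 0 and 1 has an SD of at most 0.5. At an SD of 0.35 (assumed), with empty clusters removed, one-sided power for the 63-64 point difference is still 99.5% if only 30% of cases enrol. This stands: for the planned effect, the shortfall probably does not threaten the primary test.

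**Part of the eligibility filter is addressed.** The Study Setting section says that everyone there is a regular smartphone user. That covers one criterion. It does not cover smear-positive pulmonary disease, new cases, age, the exclusions or consent.

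None of these points removes the conflict between 9 and 7 months, or the use of total incidence as the enrolled number.

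**Conclusion.** The point holds as an internal inconsistency in the stated size. The sample size uses a recruitment window at least two months longer than the one the article gives, and it treats every incident case as an enrolled patient. At the midpoint population, which is an assumption but is what yields the plan's three per cluster, the stated window gives about 43 per arm at best. That shortfall does not depend on any assumed eligible share. Figures below 43 (for example 22 at 50% enrolment) do depend on one and are illustrative. On the plan's literal inputs, one-sided power drops below 80% once modest eligibility and consent losses are added to the shorter window. With a realistic SD it does not, for the planned difference. The consequences are therefore mainly an overstated patient number and overstated precision, with fewer analysable clusters than 19 per arm expected. The validity of the comparison is not in question.

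**What to change.** In the Sample Size section, replace 9 months with the actual recruitment window, or move the recruitment end date so that the two agree. Then apply an explicit eligible and consenting fraction to the incidence, with its source or a range. Restate the expected patients per arm, the mean cluster size, the expected number of non-empty clusters, and the resulting one-sided power or detectable difference, using an SD suited to a 0-1 proportion. Do not present 57 or 70 per arm as the expected yield of the stated window, and do not describe the 20% inflation as compensating for low incidence unless time, catchment or clusters are added with it.

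The cost is a few lines of text and less favourable numbers; no extra patients are required. Extending recruitment would cost time and budget and is the sponsor's choice. The Results section says recruitment has already started, so the restatement is most useful while the end date can still change.

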### Cointerventions

The following criteria will be applied to all patients and observers, regardless of their treatment group.

Patients with pulmonary TB will be diagnosed and treated by a general physician at Hat Yai Hospital or Songkhla Hospital. After diagnosis, the patients will be referred to the TB clinic. The patients will be provided zipped bags daily for 60 days, each with a daily dose of their isoniazid, rifampicin, pyrazinamide, and ethambutol (HRZE) drug regimen [7]. Patients who consent will be registered in the database by a TB nurse. The patients will be scheduled to take their medications (HRZE regimen) once a day. After each patient registration, the observer in the jurisdiction where the patient resides will be notified through autonotification on the official LINE app (either DOT or VOT).

For monetary compensation, the patients will receive 300 baht (US $8.68) immediately after registration to cover the cellular internet cost for the first month. Further compensation will be paid once the patients complete their 60-day intensive treatment without discontinuing the assigned intervention. They will receive 300 baht (US $8.68) to reimburse the cellular internet cost for the second month and 400 baht (US $11.57) for transportation of the sputum specimen for 3 consecutive days.

The observers will be compensated 600 baht (US $17.36) if they observe medication administration among patients for at least 15 out of 60 daily sessions. They will also be compensated for the cost of travel to visit their patients (4 baht or US $0.12 per kilometer).

Apart from the assigned intervention, the care of the patients at the TB clinic will remain the same as that during routine clinical practice. In the event of any suspected adverse events, the patients or their families will be able to phone the TB clinic for advice.

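### The sample size uses a variance of 1.00, impossible for a 0–1 compliance proportion, so 80% power for 64 points does not describe this design; the error is conservative and the paragraph needs restating

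*Protocol article*

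**What the plan says.** All the inputs are in the Sample Size section of the protocol article.

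- **Variance.** "The variance was set to 1.00 as the default", and then: "The formula does not require an exact variance estimation in the population as the ICC takes the variance into account".
- **Effect.** "We assumed a difference in the cumulative compliance percentage of 64" percent, worked out as 65/100 minus 1/60.
- **VOT rate.** From a previous study, "the cumulative percentage of compliant days among patients in the VOT group was 65" percent.
- **DOT rate.** From interviews, "the patients had an actual appointment for DOT only once during the entire follow-up period", which becomes 1/60.
- **Test and power.** "We accepted 80% statistical power" and "a significance level of .05 using a one-tailed test".
- **Clustering.** ICC 0.2 and about three patients per cluster.
- **Result.** 19 clusters per arm, that is 57 patients, raised to 70.

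The same section says the design targets the compliance of observers. The outcome is defined elsewhere: the auditor scores each day 0 or 1 (the sections on VOT and DOT sessions), and a patient's daily scores are summed and divided by 60, with observer compliance built up in the same way from days observed (Primary Outcomes). No SD or variance of compliance is given anywhere in the article.

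**The concern.** Sample size for a comparison of means depends on the variance, the difference and the design effect. The ICC enters only the design effect. It is a ratio, so it is unchanged if every variance component is doubled, whereas the number of clusters roughly doubles. The sentence on variance is therefore wrong, not merely brief.

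The default of 1.00 would be harmless if the difference had been standardised, but it was not: 0.64 is a raw difference between two proportions of days. An SD of 1.00 is twice the largest SD possible on that scale.

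What is at stake is interpretation. The article ties the result to replacing DOT with VOT, and its Limitations section accepts that the comparison may be inconclusive unless DOT compliance turns out lower. To judge a small or null difference, a reader needs to know what the trial could detect, and the stated 64 points at 80% power gives the wrong answer.

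Three further features of the paragraph need correcting with it: the sidedness, the rounding of the difference, and the origin of the two planning rates.

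**Working it through.** **Inputs.** From the article: difference δ = 0.64; variance 1.00; ICC ρ = 0.2; cluster size m = 3; clusters per arm g = 19; α = 0.05; power 80%. Assumed here: equal cluster sizes, a common variance in both arms, and a t comparison with 2(g − 1) degrees of freedom. The calculator itself is not at hand.

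**Formulas.**
- Design effect = 1 + (m − 1)ρ = 1 + 2 × 0.2 = 1.4
- SE = √[2 × variance × 1.4 / (m × g)]
- Clusters per arm: g = 2 (t_α + t_power)² × variance × 1.4 / (m δ²), solved iteratively
- Detectable difference = (t_α + t_power) × SE

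**1. Reproducing the plan's figure** (δ = 0.64, variance 1.00)

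| Test | t version | Normal version |
|---|---|---|
| Two-sided 0.05 | 18.90, so **19** (power 80.2%) | 17.9, so 18 |
| One-sided 0.05 | 14.88, so 15 | 14.1, so 15 |

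The stated 19 appears only with a two-sided test. With the one-tailed test in the text, 19 clusters would have about 88% power under the plan's own inputs. On the percentage scale (δ = 64, variance 1) the formula gives less than one cluster, so the 0–1 scale was used.

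**2. Does the ICC replace the variance?** Hold ρ at 0.2 and δ at 0.64, two-sided t: variance 0.5, 1.0 and 2.0 give 11, 19 and 37 clusters. The answer is no.

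**3. Variance ceilings.** A variable on [0, 1] with mean p has variance of at most p(1 − p).
- Any mean: 0.25 (SD 0.50)
- VOT at 0.65: 0.65 × 0.35 = 0.2275
- DOT at 1/60: (1/60)(59/60) = 0.0164
- Average of the two: 0.122 (SD about 0.35)

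The plan's 1.00 is four times the absolute ceiling.

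**4. The difference.** 0.65 − 1/60 = 0.6333, that is 63.3 points rather than 64. With variance 1.00 and a two-sided test this alone gives 20 clusters, and power of 79.4% at 19.

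**5. Power of 19 × 3 per arm at feasible variances.** At variance 0.25, SE = √(2 × 0.25 × 1.4 / 57) = 0.111, so 0.633/SE = 5.7 against a critical value of 2.03 (two-sided) or 1.69 (one-sided).

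| Difference | Variance | Two-sided power | One-sided power | Clusters per arm for 80% (two-sided / one-sided) |
|---|---|---|---|---|
| 63.3 points | 0.25 | above 99.9% | above 99.9% | 6 / 5 |
| 63.3 points | 0.122 | about 100% | about 100% | 4 / 3 |
| 40 points (65% against 15/60) | 0.25 | 94% | 97% | – |

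Even with ICC = 1 and variance 0.25, two-sided power for 63.3 points is about 97%. The cluster counts below 10 are rough, because a t approximation with so few clusters and a DOT rate near zero is not exact.

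**6. Difference detectable with 80% power at 19 × 3, ICC 0.2.** With 36 degrees of freedom, t_α + t_power = 2.028 + 0.852 = 2.880 (two-sided) or 1.688 + 0.852 = 2.540 (one-sided).

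| SD | SE | Two-sided | One-sided |
|---|---|---|---|
| 0.25 | 0.055 | 16 points | 14 points |
| 0.35 | 0.078 | 22 points | 20 points |
| 0.50 (ceiling) | 0.111 | 32 points | 28 points |

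**The case against.** The strongest reply is that nothing in the trial goes wrong. The variance is too large, so the trial has more clusters than its assumptions require, and recruitment had already begun when the article was written. That stands. It limits the point to a false justification and a misdescribed power.

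A reader might go further and infer that the trial is underpowered, for instance by putting a 40-point difference into the plan's formula. The documents do not support this: the low power so obtained rests on the same impossible variance, and at the ceiling of 0.25 power for 40 points is 94% or 97%.

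A reader might also infer that 1/60 is simply not the control condition, because observers are paid "if they observe medication administration among patients for at least 15 out of 60 daily sessions" and their travel is reimbursed. That is too strong. The payment is listed among the cointerventions for both arms, a payment threshold is not an expected rate, and DOT observers are to work as in routine care. The text supports only that 1/60 may be too low for an arm with payment, weekly booklet photographs and auditor calls.

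On the VOT side, 65% is labelled a patient figure while the calculation is for observers. Since observer compliance counts the days on which each patient is observed, it is a related proxy, but the article does not say that it is one.

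**Conclusion.** The point holds and should be fixed; it does not threaten the trial's size. A variance of 1.00 is impossible for this outcome, the sentence that the ICC accounts for it is wrong, and 80% power for 64 points is not a property of the design. The calculation really targets 0.64 SD, which on the 0–1 scale is at most 0.64 × 0.50 = 0.32.

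The error is conservative: power for the assumed difference is above 99.9% at any feasible variance with ICC 0.2, and the difference detectable with 80% power is at most about 32 points two-sided or 28 one-sided. The 0.25 ceiling follows from the outcome definition alone. The other figures rest on the plan's ICC of 0.2, three patients in every cluster and 19 clusters per arm. The SD range is an assumption, because the article gives no SD.

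Secondary to this, the stated sidedness does not match the 19 clusters, the difference is 63.3 points, and the two planning rates are proxies that are not labelled as such.

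**What to change.** Rewrite the one paragraph in Sample Size:

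1. Delete the sentence saying that the ICC takes the variance into account, and the default of 1.00.
2. State the SD on the 0–1 scale as an explicit assumption, for example a range of 0.25 to 0.50, with a source if one exists.
3. State the sidedness actually used, and make it agree with the 19 clusters.
4. Give the difference as 63.3 points. Label 65% as a patient-level proxy for observers and 1/60 as a routine-care proxy for DOT, and show a range for DOT, for example 1/60 to 15/60 (differences of 63.3 down to 40 points).
5. Replace the claim of 80% power for 64 points with the difference detectable at 80% power with 19 clusters of 3 per arm and ICC 0.2: about 16, 22 or 32 points two-sided, or 14, 20 or 28 one-sided, for SD 0.25, 0.35 or 0.50.

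The cost is the rewriting. The number of clusters, the number of patients and the conduct of the trial do not change.

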### Cluster Randomized Allocation

The observers that consent to participate will be randomly allocated to either VOT or DOT by a file generated using R software (R Foundation for Statistical Computing, Vienna, Austria). The sequence will be stored in the study server. Following the protocol of this trial, the participating observers will register themselves in the study LINE system. After they press the “accept” button, the observers will be informed about their allocated intervention group through the study LINE system.

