**Methods:**

A cluster randomized controlled trial of pulmonary TB patients and their observers will be conducted over a 2-month period. This study will be conducted in the Hat Yai and Meuang Songkhla districts of Songkhla Province, Southern Thailand. A total of 38 observers working at 38 primary care units (PCUs) will be randomized equally into VOT and DOT groups. The TH VOT system will be implemented in 19 PCUs in the VOT group while the other 19 PCUs will continue with the traditional DOT program. Approximately 1-5 TB patients will be under observation, depending on the PCU jurisdiction in which the patients reside. The inclusion criteria for TB patients will be as follows: patients diagnosed with newly active pulmonary TB with a positive acid-fast bacilli sputum smear, aged >18 years, own a smartphone, and are able to use the LINE (Line Corporation) app. The exclusion criteria will be patients with a condition that requires the intervention of a specialist, rifampicin resistance according to a cartridge-based nucleic acid amplification test (GeneXpert MTB/RIF), unable to continue the treatment, and/or alcohol dependence. After the 2-month observation period, all sessions and follow-up clinical outcomes recorded will be retrieved. An intention-to-treat analysis will be performed to assess the compliance of both patients undergoing drug administration and their observers.

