## Methods

### Study Setting

This study will be conducted in the Hat Yai and Meuang Songkhla districts of Songkhla Province, Southern Thailand, where a robust internet network is available. The study setting is based on 53 PCUs in the province, each including a TB staff member who worked as a DOT observer for at least 2 years. All people in the setting are regular smartphone users.

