#### Observers (Cluster Level)

There are 53 PCUs in the study area. Based on a random list of the PCU numbers generated using R software (1-53), the observers in the PCUs numbered 1 to 38 will be randomly allocated to groups. If they refuse to undergo allocation, the observers in the PCUs numbered 39 to 53 will be subsequently invited until 38 observers have been allocated.

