### Statistical Analysis

Background information of patients and observers will be summarized using descriptive statistics.

An intention-to-treat analysis will be performed according to the randomized allocation. Thus, participants will be classified according to the intervention group to which they are assigned, regardless of their actual intervention.

We will compare the percentages of compliance between the two interventions at 60 days after treatment initiation. The 60-day compliance of the individuals will be defined as the percentage calculated using the following formula: (mean cumulative compliance days×100)/60. Our study is a cluster randomized controlled trial; thus, the cumulative number of compliant days of patients and observers will be nested in clusters. We will analyze their 60-day compliance considering that the same observer may monitor more than one patient. The intervention effect will be based on a linear mixed-effects model [22]. According to our study design, the intervention will be a fixed effect, whereas the cluster level will be a random effect.

The number of compliant days of patients and their observers will be visualized using solid green dots indicating the daily compliance of the individual subjects (Y-axis) and the elapsed number of days since starting the medication (X-axis). To investigate the dynamics of compliant days of the patients and observers over time, the mean cumulative number of complaint days within each group will also be plotted. The estimation of mean cumulative compliant days will range between 0 and 60, with 60 indicating that all participants in the group completed their daily sessions for 60 days. The function will be plotted using the mean cumulative number of compliant days (Y-axis) and the elapsed number of days since the start of medication administration (X-axis). Ideally, a steady increase in linear trend with a 45° slope indicates 100% compliance at any point from 0 to 60 days. Flattening of the slope represents a decline in the compliance percentage over time within the group.

Only descriptive statistical methods will be used on the aforementioned clinical outcomes and noncompliance activities of the observers because we may not have sufficient statistical power to detect small differences.

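### The primary model omits the district of the PCU; pre-specifying it as a fixed effect would be a cheap gain in precision, though the stated model is valid without it

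*Protocol article*

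**What the plan says.** Study Setting names two districts: "This study will be conducted in the Hat Yai and Meuang Songkhla districts of Songkhla Province, Southern Thailand, where a robust internet network is available". Cointerventions says that patients are "diagnosed and treated by a general physician at Hat Yai Hospital or Songkhla Hospital". No section says which PCUs refer to which hospital.

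The abstract fixes equal arms: "A total of 38 observers working at 38 primary care units (PCUs) will be randomized equally into VOT and DOT groups". Observers (Cluster Level) draws the clusters from one list for the whole area: "Based on a random list of the PCU numbers generated using R software (1-53), the observers in the PCUs numbered 1 to 38". Cluster Randomized Allocation says that consenting observers are "randomly allocated to either VOT or DOT by a file generated using R software". Neither section names a stratum, block or balancing constraint.

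Statistical Analysis names the terms of the model: "the intervention will be a fixed effect, whereas the cluster level will be a random effect". No district or hospital term is listed.

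**The concern.** The district of a PCU is fixed by its location and known before allocation, so adjusting for it cannot introduce post-randomisation bias. It could also plausibly matter. TB clinic nurses register patients, train VOT patients in recording, hand out the DOT booklets and remind DOT patients to return them. Many PCUs share these steps, and the steps feed the compliance score.

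With only 19 clusters per arm, an uneven split of districts between arms is not rare. If compliance differs by district, two things follow under the stated model. The district difference adds to the between-cluster variance and widens the interval, and an uneven split moves the realised estimate by a known fraction of that difference. What is at stake is precision and the credibility of one realised allocation, not the validity of the test.

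**Working it through.** **Inputs from the protocol (Sample Size):** ICC 0.2, about three patients per cluster, variance 1.00, significance level .05, 80% power, 19 clusters per arm. The section states "We assumed a difference in the cumulative compliance percentage of 64"%, entered here as 0.64; its own subtraction, 65% minus 1/60, gives 63.3%.

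**Assumptions, because the protocol gives no figure:** the number K of the 38 PCUs in one district (15 to 25), and the share f of between-cluster variance due to district (0% to 50%).

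**1. The plan's own figure.** Variance of a cluster mean = 0.2 + 0.8/3 = 0.4667. SE of the arm difference with 19 clusters per arm = √(2 × 0.4667/19) = 0.222. With t on 36 degrees of freedom, two-sided power is 80.2%, so the stated 19 per arm is reproduced. The one-tailed test named in the text would need 15 per arm, and at 19 its power is 88.3%. The two-sided figure is used below because it matches the stated 19.

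**2. Chance imbalance.** With 19 of 38 clusters drawn into one arm, the number from the district is hypergeometric. The probability that the arms differ by at least four clusters from it is:

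| K | 15 | 18 | 19 | 20 | 22 | 24 | 25 |
|---|---|---|---|---|---|---|---|
| Probability | 0.18 | 0.33 | 0.19 | 0.33 | 0.32 | 0.31 | 0.17 |

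For odd K the smallest qualifying gap is five clusters, hence the lower values.

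**3. Shift in the realised estimate.** Shift = (gap/19) × district difference. For an assumed difference of 20 points, a gap of four gives 4/19 × 20 = 4.2 points, and a 12 v 7 split gives 5/19 × 20 = 5.3 points. For 10 points, 12 v 7 gives 2.6 points.

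**4. Validity without the district term.** In a null simulation of cluster means (20,000 runs per setting, K = 19 or 24, district explaining 25% to 100% of between-cluster variance), the mean unadjusted estimate was within 0.004 SD of zero and two-sided type I error was 4.9% to 5.2%.

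**5. Precision with the district term.** Adjusted variance of a cluster mean = 0.4667 − 0.2f, with t on 35 degrees of freedom. The SE and the first power column assume districts balanced across arms. Over random allocations, the squared correlation between arm and district averages 1/37, which raises the adjusted variance by about 3%. The last column averages power over allocations.

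| f | SE, balanced | Power, balanced | Power, averaged |
|---|---|---|---|
| No district term | 0.222 | 80.2% | 80.2% |
| 0% | 0.222 | 80.2% | 79.0% |
| 10% | 0.217 | 81.9% | 80.8% |
| 25% | 0.209 | 84.4% | 83.4% |
| 50% | 0.196 | 88.6% | 87.7% |

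Break-even on variance: (0.4667 − 0.2f) × 1.03 = 0.4667 gives f of about 7%. For two districts of equal size, 0.25d² = 0.2f, so f of 10%, 25% and 50% means district differences d of 0.28, 0.45 and 0.63 SD. With an assumed patient SD of 30 points, these are about 8, 13 and 19 points.

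**6. Limit of the power figures.** They inherit the plan's variance of 1.00. A proportion between 0 and 1 has an SD of at most 0.5, so a true difference of 63.3 points would be at least 1.27 SD, or 1.27/0.222 = 5.7 standard errors. At that difference power is already near 100%, and the gain is in interval width.

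**The case against.** The strongest case against is that nothing here is an error. An intervention effect with a random cluster effect is a standard, valid analysis of a parallel cluster trial. Nothing in the article says that compliance differs by district, and some features point to similarity: good internet coverage and smartphone use throughout, common cointerventions, and one auditor working to one standard. Every size above depends on an assumed split and an assumed district effect. A shift of 4 to 5 points cannot overturn a 63-point difference, and over repeated allocations the interval already allows for it. A condensed article may also leave strata and covariates to a fuller document.

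Most of this stands, and it is why the point is only an improvement. Two parts do not remove it. First, the article names the terms of its model, so adding district changes a stated analysis and does not merely ask for detail left elsewhere. Second, the 63-point difference was planned for observers. Patient compliance is also a primary outcome, and there DOT scores are taken as reported, with over-reporting conceded under Limitations. That difference could be much smaller, and precision would then matter more.

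Three stronger readings are tempting, and the documents do not support them:
- **District imbalance biases the trial's estimate.** Randomisation keeps the unadjusted estimate unbiased, and the cluster effect carries site variation into the standard error.
- **Allocation was unstratified.** The article is silent. The single list of 53 PCUs orders the invitations; it does not describe how the 38 were then allocated.
- **District and treating hospital are the same factor.** No section maps one to the other.

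**Conclusion.** The point holds as a cheap improvement. The stated model is valid, and its type I error holds. It forgoes whatever precision district could offer and leaves a chance district imbalance in the realised allocation uncorrected. An imbalance of at least four clusters has probability 17% to 33% for 15 to 25 PCUs in one district. The benefit is modest if district explains 10% to 25% of between-cluster variance, larger at 50%, and slightly negative below about 7%. All of this rests on an assumed district split and effect, and it is small against the planned difference of about 63 points for observers.

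**What to change.** In Statistical Analysis, add the district of the PCU as a fixed effect in the primary linear mixed model for both patient and observer compliance, and report the model without it as a sensitivity analysis. Fix this before analysis: the Blinding section says that no researcher or staff member is blinded, so a later choice between adjusted and unadjusted results should not be left open. State also whether allocation was stratified by district. Allocation itself need not be revisited, since recruitment started in January 2022. Do not use hospital in place of district unless each PCU refers to only one hospital.

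The cost is one covariate in the model code, one of 36 cluster degrees of freedom, and about one point of two-sided power (80.2% to 79.0%) if districts do not differ.
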